### Randomization procedure

Participating midwife centres are randomized to include either pregnant women for the control group or for the intervention group. Randomization is stratified according to the risk of contracting a *C. burnetii *infection as determined by the number of goat farms in the neighbourhood (registration by Statistics Netherlands (CBS)), and by the size of the midwife centre.

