### Data collection

Data will be collected in four ways using a structured case record file:

**1. Serological samples **will be collected at the time points described in the section Experimental procedure, and will be analyzed in the laboratory of the Jeroen Bosch Hospital.

**2. Questionnaires**; two questionnaires will be filled out by the participant and one will be filled out by the midwife/obstetrician.

At baseline, when the participant is included in the trial, a questionnaire is completed by all participants including questions about the current pregnancy, outcome of previous pregnancies, smoking and alcohol habits, co morbidities, medication use and demographic characteristics. With this questionnaire risk factors are assessed for complicated pregnancy outcome. After delivery all relevant outcome data on obstetric complications are collected by a questionnaire completed by the midwife. Questionnaires for participants who are referred to a hospital during pregnancy or delivery, are filled out by the obstetrician. During follow up, all health care and potential cost data will be measured by a third questionnaire completed by the participant one month after delivery. With this questionnaire we will also verify symptoms during pregnancy, health-related quality-of-life (using EQ5D [15]), depressive symptoms and fatigue (using the Shortened Fatigue Questionnaire [16]), potential long-term consequences of Q fever, tolerance to antibiotic treatment and problems and development of the newborn. Furthermore, the risk for Q fever infection will be assessed.

**3. PCR and histo-pathology of the placenta **will be performed by the local microbiologists and pathologists. Re-evaluation of the histological slides will be performed by one pathologist at the University Medical Centre Groningen.

**4. Medical data in primary care; **data on the health status of the participant or the newborn is collected from medical files of the general practitioner.

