### Sample size calculation and statistics

Based on the literature and pilot data from The Netherlands, we expect that 12% of pregnant women in the high-risk areas will have serological evidence for a Q fever infection [17,18]. Of these women, we conservatively estimate that 25% will develop complications, so 3% of women will have the primary outcome. Assuming a reduction of the complication rate of 50% by early detection with screening during pregnancy, we will need a participation of at least 3,400 participants with complete follow up (statistical power of 80 percent, p ≤ 0.05). Assuming a loss to follow up of 10% and to allow for a small clustering effect, we aim to include 4,000 participants.

Data will be analyzed according to intention-to-screen principles. A two-sided p-value of 0.05 or less will be considered to indicate statistically significant. Descriptive statistics concerning the distributions of the predictor variables and outcome variables will be performed using the software SPSS for windows (version 16). For univariate analysis the chi-square test and Fischer's exact test will be used to compare proportions. For variables with a normal distribution, differences will be analysed with Student's t-test. In case of non-parametric distribution, differences between populations will either be evaluated using the Mann-Whitney-U test or the data will be log-transformed to obtain a normal distribution. Relative risks as well as absolute risk reductions and numbers needed to treat will be estimated with their corresponding 95% confidence intervals. Possible clustering of outcome data will be taken into account using generalised estimating equations (GEE) modelling.

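### In a trial that randomises midwife centres within strata, the plan lists tests for independent women beside GEE, does not say which gives the primary result, and gives the strata no role.

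*Protocol article*

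**What the plan says.** Under Randomization procedure, the Protocol article makes the centre the unit of allocation: "Participating midwife centres are randomized to include either pregnant women for the control group or for the intervention group". Allocation is stratified by infection risk, "determined by the number of goat farms in the neighbourhood", "and by the size of the midwife centre".

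Under Sample size calculation and statistics, the analysis is set out in this order:

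- intention-to-screen, with a two-sided 0.05 threshold;
- descriptive statistics, in a sentence of their own;
- "For univariate analysis the chi-square test and Fischer's exact test will be used to compare proportions";
- Student's t-test for normally distributed variables, and otherwise Mann-Whitney or a log transformation;
- relative risk, absolute risk reduction and number needed to treat with 95% confidence intervals, with no model named;
- "Possible clustering of outcome data will be taken into account using generalised estimating equations (GEE) modelling".

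The same section sizes the trial on 3% of all women having the primary outcome (12% seropositive, 25% of those with complications) and a 50% reduction. This gives 3,400 women with complete follow-up, raised to 4,000 for 10% loss and a small clustering effect. Under Outcome measures, the primary endpoint is defined in Q fever positive women.

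**The concern.** When centres are randomised, clustering is a feature of the design. The analysis has to reflect it whatever correlation is later observed, so calling it *possible* sets the wrong default. It is also to be expected here: stratifying by nearby goat farms presumes that infection risk differs between centres, and the 3% outcome rate is built directly on seroprevalence.

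The simple tests treat women as independent and are not confined to description. The 0.05 threshold and the effect intervals are attached neither to them nor to the GEE. Two analyses of unequal validity could therefore answer the primary question, with nothing fixed in advance to say which one counts.

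The strata raise a separate issue that runs in the opposite direction. Stratified allocation balances the arms on goat-farm risk and centre size. An analysis that ignores those factors does not take credit for that balance, so its standard error is too large where the strata predict outcome.

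**Working it through.** **Inputs from the Protocol article.** Risks 3% and 1.5%, two-sided 0.05, 80% power, 3,400 completers, 10% loss, 4,000 recruited. **Assumed, because the article does not give them:** 1:1 allocation, 40 to 100 centres, intracluster correlation (ICC) 0.005 to 0.01, and the strength of the strata.

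**1. The plan's own figure.** The two-proportion formula with pooled variance gives 1,534 per arm, or 3,068 in total. With continuity correction it gives 1,664 per arm, or 3,328 in total, which is within 3% of 3,400. So 3,400 is a sample size for individually randomised women.

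**2. Room left for clustering.** 4,000 × 0.9 = 3,600 completers, and 3,600 / 3,400 = 1.059. The implied design effect is about 1.06.

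**3. True error rate of a test that ignores centres.** With m women per centre, DE = 1 + (m − 1) × ICC, and true alpha = 2 × [1 − Φ(1.96/√DE)].

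- At the implied DE of 1.059: 1.96/1.029 = 1.905, so alpha = 0.057.
- For 3,600 completers:

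| Centres | m | ICC | DE | True alpha | √DE |
|---|---|---|---|---|---|
| 100 | 36 | 0.005 | 1.175 | 0.071 | 1.08 |
| 100 | 36 | 0.01 | 1.35 | 0.092 | 1.16 |
| 60 | 60 | 0.005 | 1.295 | 0.085 | 1.14 |
| 60 | 60 | 0.01 | 1.59 | 0.120 | 1.26 |
| 40 | 90 | 0.005 | 1.445 | 0.103 | 1.20 |
| 40 | 90 | 0.01 | 1.89 | 0.154 | 1.37 |

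The last column is the factor by which a correct interval is wider than the simple one. From ICC = CV² × p/(1 − p) at p = 0.03, these ICCs correspond to a between-centre coefficient of variation (CV) of about 0.40 to 0.57 in outcome risk.

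**4. Effect of stratified allocation and of the denominator.** These are null simulations with 25% complication risk in both arms, seroprevalence CV 0.3/0.5/0.75 between centres, 4,000 trials per setting and six assumed strata. The figures are chi-square error rates.

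| Setting | 90 centres × 40 women | 60 centres × 60 women |
|---|---|---|
| All women, unstratified | 6.0/8.6/11.7% | 6.6/10.6/15.4% |
| All women, strata explain half the between-centre variance | 5.0/7.4/9.5% | 5.7/7.6/11.1% |

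If the strata explain 80% of the variance, the rate is 5.7% to 6.8% in all settings. Restricted to Q fever positive women, it is 4.7% to 5.4% in all settings, because the model gives every positive woman the same risk.

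**5. Cluster-robust test with and without the strata.** This is a null simulation with stratified allocation, four assumed strata, 40, 60 or 100 centres, ICC 0, 0.005 or 0.01 within strata, and 4,000 trials per setting.

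| Analysis | Strata unrelated to outcome | Four-fold risk range across strata |
|---|---|---|
| Robust, strata omitted | 0.044–0.053 | 0.014–0.037 |
| Robust, strata included | 0.045–0.054 | 0.048–0.058 |

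The robust test holds its level when the strata are in the model. It becomes conservative when strongly prognostic strata are left out.

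**The case against.** The strongest reply is that the sentence on GEE is itself the remedy. Its verb is unconditional, the simple tests are introduced as univariate, and the recruitment target already allows for a small clustering effect. A crude comparison followed by a clustered model is a natural reading. This stands in part. The plan does not ignore clustering, and a reader who infers that its intervals and p-values will be wrong goes further than the text. They would be wrong only if the simple tests supplied them, and the text leaves that open.

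A second reply is that the larger error rates depend on assumptions. This also stands. Centre numbers and ICCs are not in the article, stratified allocation removes the share of between-centre variation that the strata explain, and a comparison among positive women only showed no inflation under constant risk. The all-women comparison is nevertheless the one the trial was sized on.

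A third reply is that model terms belong in the analysis plan, which is not shown. For baseline covariates this is right. A reader might infer that the risk factors collected by questionnaire will go unused, or that imbalance is likely because midwives at allocated centres invite the women. The article supports neither: it is silent on adjustment, and it says that researchers carry out the consent procedure. The choice of primary analysis is different, because the article does list the tests and leaves them unranked.

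Finally, it is tempting to count the omitted strata as another source of intervals that are too narrow. Step 5 of the working shows the opposite.

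**Conclusion.** The point holds as a defect in how the primary analysis is fixed; adjustment for clustering is not absent. The statistics section puts tests for independent women beside a GEE, treats clustering as contingent, does not tie the primary p-value or the effect intervals to either, and gives the randomisation strata no role.

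If the simple tests were used on all women, the true error rate would be about 5.7% at the plan's own implied design effect, and about 7% to 15% for ICC 0.005 to 0.01 with 40 to 100 centres. Correct intervals would then be about 1.08 to 1.37 times as wide. These figures rest on assumed centre numbers and ICCs and on an all-women denominator. They fall towards 5% as the strata explain more of the variation, or if only positive women are compared.

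If the GEE were used without the strata, validity would be kept but power would be lost where the strata are prognostic (simulated size 0.014 to 0.037 under an assumed four-fold range). Little room for clustering was left in the sample size, so that loss is worth avoiding.

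**What to change.** Before the data are analysed:

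- Delete *Possible* from the sentence on clustering.
- Name one primary analysis: a GEE with midwife centre as the cluster, robust standard errors, and arm, goat-farm-risk stratum and centre-size stratum as fixed terms.
- Take the primary p-value and the intervals for the relative risk, absolute risk reduction and number needed to treat from that analysis. If an identity link does not converge, which is a real possibility at risks of 3% and 1.5%, obtain the absolute risk reduction by standardisation from the fitted model.
- Use chi-square, Fisher, t and Mann-Whitney tests for description only.

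Further baseline covariates are optional and can be left to the statistical analysis plan.

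The cost is a paragraph of text, since centre and strata are known from the randomisation and no new data are needed. The downside is that p-values may be slightly larger than chi-square would give.

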### Economic evaluation

The study will primarily provide insights into the economical balance of undetected and detected Q fever during pregnancy. The economic evaluation will be performed from a societal and health care perspective. Direct medical and non-medical costs (laboratory costs, costs of health care following positive screening, time, and travel costs) as well as indirect costs (loss of productivity) will be taken into account. The time horizon will be from taking the blood sample until one month after delivery for measured and calculated costs and until one year after delivery for estimated costs. Data on health care use and productivity loss will be collected by questionnaires. Unit costs will be based on the Dutch 2004 guidelines for costing in health care research and indexed for base year 2010 using yearly general consumer price indices [19].

## Discussion

Right at the beginning of the first Q fever outbreak in The Netherlands in 2007, the government and health care providers assessed the risk of Q fever related to the outcome of pregnancies [20]. In all, only research from France is currently available on the risks of Q fever during pregnancy and the benefits of long-term antibiotic treatment [10]. There is, however, a lack of data on the prevalence and the risk of Q fever infection and the impact of antibiotic treatment during pregnancy in other countries such as The Netherlands. Therefore, in December 2008 the Dutch Health Council advised the Ministry of Health not to screen for Q fever during pregnancy until additional scientific data would be available to support screening [20]. The Dutch outbreak is an opportunity to gain more knowledge in this field. Therefore we will conduct the study described previously, to provide insights into the balance of risks of undetected and detected Q fever during pregnancy. By the end of February 2011 all data will be available for analysis. First results are expected in spring 2011.

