### Inclusion criteria

Pregnant women, 18 years of age or older, with an estimated date of delivery between June 1^st ^and December 31^st ^2010, and under supervision of a midwife in primary health care are eligible for inclusion. In The Netherlands, midwives working in primary health care are allowed to only supervise uncomplicated, singleton pregnancies. It is estimated that approximately 10,000 eligible pregnant women live in the Q fever affected areas.

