**Figure 2 F2:**
[figure not shown]
**Idealised antibody responses in acute Q fever as measured by IFA^13^**.

In case of acute Q fever, the participant will be referred to an obstetrician, and treatment will be advised according to the local hospital protocol. In the literature, the first choice treatment of Q fever during pregnancy is oral cotrimoxazole (sulfamethoxazole/trimethoprim) for at least 5 weeks [10]. Antibiotic treatment, further obstetrical care and serological follow up will be supervised by the obstetrician in collaboration with the medical microbiologist. The current routine for pregnant women being treated for acute Q fever is to perform monthly blood analyses to detect the development of chronic Q fever. If the titres decline, the frequency of these controls is scaled down to once every two months during pregnancy, and at 3, 6 and 12 months after delivery. If chronic Q fever develops, treatment will be continued until the end of pregnancy followed by bactericidal treatment with doxycycline and hydroxychloroquine after delivery. In Q fever cases placentas will be collected for polymerase chain reaction (PCR) and histo-pathology.

If there is evidence for a past infection, no treatment is started. However, midwives will be advised to perform an extra serological analysis later in pregnancy to exclude reactivation.

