### Outcome measures

The primary endpoint is a maternal (chronic Q fever or reactivation) or obstetric complication (low birth weight, preterm delivery or fetal death) after the first trimester of pregnancy in Q fever positive women.

The secondary endpoints are direct and indirect costs of the screening program compared to costs of complications which could be prevented by screening. Furthermore, we aim to assess the course of infection in pregnant women, the accuracy of the diagnostic tests used for screening, histo-pathological abnormalities of the placenta of Q fever infected women, and side effects associated with treatment.

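### All data are promised by end February 2011, but the serology for chronic Q fever, part of the primary endpoint, runs to 12 months after delivery in treated women due as late as 31 December 2010

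*Protocol article*

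**What the plan says.** Five statements in the protocol article bear on this point.

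- **Outcome measures:** "The primary endpoint is a maternal (chronic Q fever or reactivation) or obstetric complication". Counting starts after the first trimester. No end is given.
- **Experimental procedure, Intervention group (text after Figure 2):** the routine for women treated for acute Q fever is to "perform monthly blood analyses to detect the development of chronic Q fever". If titres fall, "the frequency of these controls is scaled down to once every two months during pregnancy, and at 3, 6 and 12 months after delivery".
- **Data collection, item 1:** serological samples "will be collected at the time points described in the section Experimental procedure".
- **Inclusion criteria:** women are eligible "with an estimated date of delivery between June" 1 and 31 December 2010.
- **Discussion:** "By the end of February 2011 all data will be available for analysis". First results are announced for spring 2011.

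The Control group section adds that stored serum is tested after delivery. If it is positive, the general practitioner is advised to repeat serology to rule out chronic disease. No date is set for that test.

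**The concern.** These statements cannot all hold. Chronic Q fever counts towards the primary endpoint, and the samples meant to find it are trial data. The last of those samples falls well after the date on which all data are said to be available.

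If the February 2011 date is followed, the time in which chronic Q fever can be found depends on when a woman is due. A treated woman due in June could contribute 3-month and 6-month samples, and one due in late December could contribute neither. Two women with the same course of infection could then be classified differently on the primary endpoint because of the calendar alone.

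**Working it through.** **Inputs.** Due dates run from 1 June to 31 December 2010 (Inclusion criteria). Data are available by the end of February 2011, taken as 28 February (Discussion). Post-delivery samples fall at 3, 6 and 12 months (Experimental procedure, Intervention group). Delivery is taken to occur on the due date. One month is 30.4375 days.

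**Step 1: observation time after the due date** = 28 February 2011 minus due date.
- Due 1 June 2010: 272 days; 272 / 30.4375 = 8.9 months.
- Due 31 December 2010: 59 days; 59 / 30.4375 = 1.9 months.

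**Step 2: length of the due-date window.** June to December has 30 + 31 + 31 + 30 + 31 + 30 + 31 = 214 days.

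**Step 3: share of due dates for which each sample falls by 28 February 2011.** The documents do not give the distribution of due dates, so an even spread is assumed. The share is the number of days from 1 June to the latest qualifying due date, divided by 214.

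| Sample | Latest qualifying due date | Days in window | Share |
|---|---|---|---|
| 3 months | 28 November 2010 | 181 | 181/214 = 85% |
| 6 months | 28 August 2010 | 89 | 89/214 = 42% |
| 12 months | 28 February 2010 | 0 | 0% |

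The 0% does not depend on the even spread, because the latest qualifying date lies before the window opens.

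**Step 4: when the schedule would end.** For a due date of 31 December 2010, the 12-month sample falls around 31 December 2011, ten months after the stated date.

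**Step 5: who is on this schedule.** The 3-, 6- and 12-month samples apply to women treated for acute Q fever whose titres decline. On trial procedures, these are mainly detected cases in the intervention arm. Women with a past infection are advised to have one further test later in pregnancy. Control positives have the one undated test through the general practitioner. The shares in Step 3 therefore describe women on the schedule and not all participants.

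**Step 6: sample size.** The stated 3,400 comes from 3% versus 1.5%, two-sided 0.05 and 80% power. The standard formula gives 1,534 per arm (3,068 in total), and 1,664 per arm (3,328) with continuity correction, which is within 3% of 3,400. The calculation has no term for follow-up time, so the date conflict does not change it.

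**The case against.** The strongest defence is that February 2011 fits most of the data. The last participant questionnaire is due one month after delivery, measured costs stop at one month, and costs to one year are explicitly estimates. The last due date plus one month, plus time to collect forms, gives roughly the end of February. This stands for the obstetric outcomes, the questionnaire and the costs. It does not cover the serology, which the Data collection section ties to the time points in the Experimental procedure section.

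A second defence is that the 12-month follow-up is only routine care. The article does describe it as current routine, but the same Data collection sentence brings it into the trial.

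A third is that the date is one timeline sentence and not a rule for locking the database, and that a fuller protocol may define the window. It is true that the cut-off is inferred from the calendar. No fuller document, however, could make a 12-month sample available by February 2011 from a woman who delivers in the eligible period.

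A reader might go further and infer three things that the documents do not support.

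- **That controls lose more cases, so the comparison is biased in a known direction.** Controls have no 3-, 6- and 12-month schedule to lose. The scheduled samples cut off by the date are mainly in treated women of the intervention arm, which would lower the count there. Late tests by general practitioners could also be missed, which would lower the count in controls. The article does not say how soon those tests are done, so the net direction is unknown.
- **That the date causes the unequal testing intensity between arms.** That difference comes from the procedures for the two groups and would remain with any later cut.
- **That the primary result loses a known number of events or amount of power.** The article does not give the share of the assumed 25% complication rate that is chronic Q fever, so the loss cannot be sized.

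**Conclusion.** The point holds for one component of the primary endpoint. For the scheduled serology on chronic Q fever, the claim that all data will be available by end February 2011 contradicts the article's own follow-up schedule. At that date, observation after the due date ranges from 8.9 to 1.9 months. Among women on the schedule, about 85% reach the 3-month sample, 42% the 6-month sample and none the 12-month sample.

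The first two shares assume evenly spread due dates and delivery on the due date; earlier or later delivery would move the figures by some weeks. The consequence is that ascertainment of chronic Q fever depends on the due date. Due dates should be distributed similarly in the randomized arms, so this unevenness does not by itself favour either one. The effect on the comparison is of unknown direction and size. This should be put right before the data cut, but it does not undermine the obstetric part of the endpoint.

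**What to change.** Reconcile the sections on outcome measures, experimental procedure, data collection and timeline. Define one post-delivery window within which chronic Q fever counts towards the primary endpoint, the same in both arms and completed by every woman before the primary data cut. There are two ways to do this:

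1. **Move the cut for this component** to the day the last-delivering woman completes the window. For a due date of 31 December 2010, a 3-month window ends around 31 March 2011, a 6-month window around 30 June 2011 and a 12-month window around 31 December 2011.
2. **Keep February 2011** with a window that all women complete, and report chronic Q fever found later as a secondary outcome from a second data cut. For the last due date the window could be at most 59 days, less any days by which delivery runs late. All the 3-, 6- and 12-month samples would then fall outside the primary endpoint.

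In either case, record the date of each post-delivery test, including the general practitioner's test in controls, so that the window can be applied.

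The cost is protocol wording and either a later report or a two-step report. The clinical follow-up schedule need not change, and which schedule is right is not judged here. A common window does not by itself remove the difference in testing intensity between the arms.
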